### 1.3.2. Rationale for using parent and patient reports to measure patient outcomes

The primary study goal is to evaluate the effects of PQ Response on patient HRQoL and symptom burden across a wide age range of children, adolescents, and young adults (AYA). While self-report remains the gold-standard for these type of outcomes, there is an increasing body of evidence suggesting that in the case of children/AYA there is considerable value in having both parent and child/AYA reports. Each informant in the parent-patient dyad provides a unique perspective, influenced by their experience, personal characteristics, role, and environmental aspects, among others. Together, these reports provide a broader picture of the child/AYA's situation. Yet, one of the consequences of using "multiple informants," is that the information may be non-concordant (divergent). The optimal approach to consolidate multiple informant responses into a unique child/AYA outcome is still unresolved. Acknowledging the clinical importance of considering both "voices" (i.e. patient and parent), we will measure patient outcomes (HRQoL and symptom burden) using both parent and patient reports. The chosen instruments allow parental report across the study's full age range, and patient self-report from the age of five for HRQoL, and from the age of 7 for symptom burden (however, because the younger child version of the symptom instrument for ages 7-12 does not measure the full range of symptoms we will not use it as an outcome measure, see section 2.4.2.1 for details). Given the lack of consensus as to how to handle multiple informant information, the effects of the intervention on patient outcomes will be analyzed separately for each of these informants. Of note, the data collected in this trial will also provide the opportunity to explore convergence and divergence of child/AYA and parent reports.

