Participants' adherence to study procedures will be facilitated by a relatively short follow-up, flexibility in scheduling interviews, and working with experienced RCs (in at least two of the sites the RCs have already worked in prior or related projects of this group). Adherence with the PQ system will be enhanced in both arms through the automated emails/notifications sent to participants reminding them to fill in their assigned surveys. In addition, when a participant/family does not answer a PQ-Survey or declines to meet with Response team, RCs will contact the family over their preferred route of contact (phone or email) to discuss any difficulties and their willingness to continue participation. As a token of appreciation, the patient and one parent will each receive a \$40 Amazon gift card for every 4 weeks of study participation. \$20 dollars will be provided to patient and one parent for participating in the two-week run-in period.

Participants' adherence will be monitored by the PM during study meetings (recurrence of these meetings will be flexible, with at least a monthly meeting). If either parent or child misses four consecutive PediQUEST surveys, the dyad will be removed from the study. Rare exceptions to this criterion may be granted at the discretion of the PI and PM.

| Process                                     | Indicators                                                                                                                                                                                                                    | Source                     | Period  | Target |
|---------------------------------------------|-------------------------------------------------------------------------------------------------------------------------------------------------------------------------------------------------------------------------------|----------------------------|---------|--------|
| Intervention component                      | 1. No. Times Visit Occurs within 3 wks randomization/ No. randomized to intervention                                                                                                                                   | MR*                        | Monthly | >90%   |

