### 2.3.3. Rationale for intervention's "dose," frequency, and administration:

Weekly PQ-Surveys: Surveys will be administered weekly to capture distress in real time. A longer interval may make the intervention less relevant if surveys miss the distress event or participants answer about distress that occurred longer ago. Ideally, one would want participants to report distress on an "as needed" basis, however this approach is challenging from a design point of view as controls may have less incentive to report. For this reason, we decided to collect weekly measures in both arms. Weekly reporting allows the Response team to intervene and propose prevention strategies if symptoms are thought to be recurrent. During the pilot, adherence to weekly surveys was good; over 75% of participants answered 50% of weekly surveys or more, and 60% answered 75% of weekly surveys or more.

Response team intervention: Response teams will contact the families: (i) on a regular basis over the intervention period (we encourage at least monthly encounters), (ii) to attend to PQ reports, and (iii) to monitor treatment recommendations. Regular contacts are proposed as a means of standardizing the intervention across patients with varying experiences of distress.

Response teams will be informed of criteria for potential distress including:

- a. a PQ-MSAS total score of 3.2 or higher (for children using PQ-MSAS 7-12 (see section 2.5.1.) the equivalent threshold value is 9) or individual symptom scores of 50 or more, or
- b. PedsQL total score below 60.

A PQ-MSAS score of 3.2 (or 9) was chosen as a threshold because it is the minimum score that includes one severe symptom (i.e. that participant reported at least two of the following characteristics for a given symptom: it is very severe, or happens almost all the time, or bothers him/her a lot or very much). It could also represent a report with five mild or moderate symptoms, which also warrants evaluation. In addition, teams will be advised that any symptom score of 50 or more may indicate current or past distress. Similarly, the score of PedsQL of 60 denotes a poor quality of life (this represents approximately one standard deviation below the average PedsQL score in pediatric cancer populations). These threshold scores will promote optimal Response team intervention. Further, this approach helps standardize the response to distress and as such increases replicability of the intervention.

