## 2.4. Outcomes

### 2.4.1. Primary Outcome Measures (aim 1)

Child Quality of Life: Difference between the two treatment arms in the mean over 16-weeks (16-w) of PedsQL total score as reported by (a) the parent for all enrolled patients, and (b) the patient if 5 years of age or older. PedsQL scores range from 0-100 (higher better) and are calculated as the average of all 22 items (total score). For each weekly administration, scores are calculated if >50% of the PedsQL items are answered. Treatment success will be defined as a difference of at least the minimal clinically important difference (MCID) between groups. The MCID for PedsQL total score is 4.4 points.

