### 3.2. Blinding

After randomization, participants, PC team, oncologists, and research staff will be unblinded to group assignment, because the intervention is not amenable for blinding.

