## 4.3. Statistical methods

### 4.3.1. Overview

All statistical analysis will be conducted on an intention-to-treat basis, i.e. all randomized participants with baseline and at least one post-baseline measurement will be analyzed by original treatment assignment, regardless of adherence. Baseline characteristics will be described and compared between groups using summary measures (e.g. means, medians, rates) and tests selected based on variable distribution. Analyses will be adjusted for factors used in the stratified randomization (center, age group and type of cancer). In addition, if, despite efforts to standardize intervention delivery (section 5.1), we identify substantial differences in fidelity across sites, we will evaluate effect modification by site including the site  $\times$  intervention interaction in the models. The False Discovery Rate criterion will be used to correct for multiple testing in non-planned analyses. Co-I [name] has been the primary biostatistician for all prior PQ analyses and is best suited to head the PQ Response's analysis, along with her team at Deakin University. The PI and Co-I [name] will be part of the leadership team. While all Co-Is will be involved in analysis and manuscript writing, some may take a more prominent role according to their specific expertise (e.g. [name], [name] with aim 2, and [name] with aim 3). DFCI will coordinate data cleaning and programming.

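### Removing a randomised dyad when either member misses four weekly surveys ends follow-up of an informant who may still be answering, and risks informative missing data

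*Protocol*

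**What the plan says.** Protocol section 2.3.2 (Adherence) sets the rule for both arms: "If either parent or child misses four consecutive PediQUEST surveys, the dyad will be removed from the study". It adds: "Rare exceptions to this criterion may be granted at the discretion of the PI and PM". No criteria for an exception are given. The same section provides a safeguard before that point. When a survey goes unanswered, "RCs will contact the family over their preferred route of contact (phone or email) to discuss any difficulties and their willingness to continue participation".

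Section 2.4.1 defines the primary outcome as the between-arm difference in the 16-week mean of "PedsQL total score as reported by (a) the parent for all enrolled patients, and (b) the patient if 5 years of age or older". Section 1.3.2 says that "the effects of the intervention on patient outcomes will be analyzed separately for each of these informants".

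Section 4.3.1 defines the analysis as intention to treat. Randomised participants with a baseline and at least one later measurement "will be analyzed by original treatment assignment, regardless of adherence". Section 4.3.2.1 uses a mixed linear model with categorical time. Section 4.3.3 plans imputation or weighting under missing at random, and sensitivity analyses otherwise. Section 3.2 says that, among others, "research staff will be unblinded to group assignment".

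**The concern.** The run-in already screens out non-responders before randomisation. Section 2.3.2 goes further and turns non-response after randomisation into removal of the whole dyad. Three things follow.

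- **The trigger is wider than any analysis needs.** Each primary analysis uses one informant. A child who goes silent for four weeks ends the parent's series as well, and a silent parent ends the child's.
- **Outcomes unrelated to the trigger stop too.** Parent anxiety and depression (every four weeks), symptom-related stress and Brief-COPE (needed at week 16) and psychosocial encounters (from the chart) do not depend on the child's survey. Nothing says that they continue after removal.
- **The removed dyads may not be a random subset.** A long silence may accompany a change in the child's health, and exceptions are decided with knowledge of the arm. If removal is related to health, the weekly scores that remain are a selected set, and the 16-week mean difference can be biased in either direction. Section 4.3.3 can model missing data but cannot recover scores that were never requested.

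**Working it through.** **1. The plan's own figures.** Section 2.6.1 gives 85% power for 68 per arm, difference 4.4, SD 9.5, one-sided alpha 0.05.
- Standardised difference: 4.4 / (9.5 × √(2/68)) = 2.70.
- Power: Φ(2.70 − 1.645) = 85.4% (85.1% with the t distribution). The stated figure reproduces.
- Attrition in section 2.6: 150 × 0.90 = 135, against 136 stated.

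**2. What one removal costs.** There are 16 weekly post-randomisation surveys. If removal follows week 4, the other informant loses up to 16 − 4 = 12 scores (75%). If it follows week 8, the loss is up to 8 scores (50%). Under section 2.5, children aged 2 to 4 do not answer surveys, so this loss of a second informant applies only from age 5.

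**3. How many dyads could be removed.** The document gives neither a weekly miss rate nor the clustering of misses. Section 2.3.3 gives only pilot bands: over 75% of participants answered at least half of the surveys, and 60% answered at least three quarters. The inputs below are therefore assumptions: weekly miss rate *m* of 15% or 25%, and lag-1 correlation *r* of 0 or 0.3 between one person's successive weeks.

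A two-state Markov chain has
- P(miss | missed last week) = m + r(1 − m)
- P(miss | answered last week) = m(1 − r)

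For m = 0.15 and r = 0.3 these are 0.405 and 0.105. For m = 0.25 and r = 0.3 they are 0.475 and 0.175. Let p be the exact probability of at least one run of four misses in 16 weeks. A dyad is removed with probability p if there is one informant or if the two miss together, and with probability 1 − (1 − p)² if they miss independently.

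| m | r | One informant, or two fully linked (p) | Two independent informants |
|---|---|---|---|
| 15% | 0 | 0.6% | 1.1% |
| 25% | 0 | 3.9% | 7.6% |
| 15% | 0.3 | 8.0% | 15.3% |
| 25% | 0.3 | 18.8% | 34.0% |

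The either-member trigger roughly doubles a small single-informant risk when the two are independent (3.9% to 7.6%) and adds nothing when they are fully linked.

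**4. Bound on the loss of power.** Suppose removed or lost dyads contributed no data at all, which overstates the loss. Starting from 75 per arm, one-sided power would be 85.2% at 10% total loss, 81.4% at 20% and 76.7% at 30%. Power is the smaller issue; the larger one is which scores are missing.

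**The case against.** Several stronger readings are tempting, and the document does not support them.

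- **That recorded data are thrown away.** Nothing says that scores collected before removal are deleted. Section 4.3.1 keeps anyone with a baseline and one later measurement. Only future collection stops.
- **That the rule contradicts intention to treat outright.** The wording in section 4.3.1 governs analysis by assigned arm. The rule reassigns nobody and excludes nobody with usable data. It does stop follow-up because of non-adherence to surveys, which sits badly with the aim of that section.
- **That missingness is known to depend on arm or illness.** No section reports this, and the rule is identical in both arms. The remark in section 2.3.3 that "controls may have less incentive to report" concerns an as-needed reporting scheme that was rejected. Weekly surveys in both arms are the stated remedy, so the remark is not evidence about the weekly surveys.
- **That the rule alone uses up the 10% attrition allowance.** The shares above depend on assumed miss rates and correlations. Many four-week non-responders may be the same dropouts already counted in section 2.6. Parent and child misses are also likely to be linked, especially at ages 5 to 7, where the child's survey goes to the parent's account.

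There are real mitigations: automated reminders, coordinator contact after a missed survey, completion by telephone or on the research tablet, monthly reporting of dropouts and reasons, exit interviews that inform the missing-data approach, and the sensitivity analyses in section 4.3.3. They lower the chance of reaching four misses, or help to explain it. None of them keeps a willing informant in follow-up once the rule is applied.

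**Conclusion.** The point holds in a limited form. As written, the rule ends future collection from an informant who may still be answering (up to 12 of 16 weekly primary-outcome scores, for children aged 5 or older). Because no continuation is stated, it also ends the parent's monthly and week-16 outcomes and the chart abstraction. The mixed model can use intermittent responses, so removal brings no analytic gain. Informative missingness, possibly differing by arm, is a risk and not a documented fact.

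The share removed is not derivable from the document. Under assumed weekly miss rates of 15% to 25%, it is about 1% to 8% of dyads with independent weeks and about 8% to 34% with lag-1 correlation 0.3, depending on how closely parent and child misses are linked. These ranges illustrate exposure and do not predict it. The conclusion does not rest on them: data not collected cannot be recovered, the trial is small, and the loss is avoidable.

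**What to change.** Separate survey non-response from withdrawal in section 2.3.2.

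- Replace the removal rule with continued automated weekly and monthly surveys from any willing informant, and continued chart abstraction, to week 16, unless consent is withdrawn or the child dies. One member's silence should not stop the other's surveys.
- Keep the existing coordinator contact after missed surveys.
- State that all scores from dyads already removed are analysed in the assigned arm.
- Report removals and exceptions by arm, with reasons.

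The cost is a short amendment and a few more reminders and gift cards. Survey assignment and reminders are already automated. Data not collected from dyads already removed cannot be restored, so the report should show how many there were in each arm.

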management skills (especially non-pharmacological strategies). Response teams are expected to maintain fluid and direct communication with the primary oncology team (P.O.T.) via email, phone or face-to-face to discuss their findings and recommendations. Ultimately, the P.O.T. will hold the decision to implement recommendations. Whenever recommendations are made (by P.O.T. or Response team) a designated member of the Response team will follow-up with the family to assess results and make further recommendations/contact P.O.T. as necessary. In the event that after following the proposed plan, there is a lack of adequate response (increase or no change in symptom scores or indication by patient or parent that relief is not sufficient), Response teams are encouraged to meet with local PIs to discuss the case. In addition, the confidential PediQUEST listserv will be available for use by Response team members (see below in Support). All communications and visits will be documented in charts. Once the proposed follow-up is completed, participants in the intervention arm will be offered the opportunity to continue being followed by the PC team (it will be clearly explained that use of PediQUEST web will be discontinued at this point).

At each site, research staff and the Response team will complete a schema to identify Response team members in charge of different aspects of the intervention. Specifically, the schema will indicate who will be alerted about new participants, who will receive the notice to schedule an initial visit, who will be responsible for initiating conversations with the P.O.T., who will receive PQ reports and distribute them to other team members, and who will be in charge of patient follow-up when recommendations are made. We expect that there will be two people in direct contact with the RC, one with a stronger administrative role and one with a clinical role (Figure 7). However, team members can be responsible for one or more tasks, structure may vary according to the organization of PC teams, and should be regularly revised to accommodate team rotation or other changes.

[figure not shown]

**Figure 7. Early Integration of the Response Team Activities.** Main activities of early integration component are depicted in the figure.  

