|                                             | 2. No. Times Symptom history addressed* in initial or next visit / No. randomized to the intervention                                                                                                                  |                            |         | >90%   |
|                                             | 3. No. Times "Your Child QOL matters" material handed to family and discussed* / No. randomized to the intervention                                                                                                    |                            |         | >80%   |
|                                             | 4. No. Times RT communication with primary team documented* / No. randomized to intervention                                                                                                                           |                            |         | >90%   |
|                                             | 1. No. of contacts of RT w/family or POT after a report of distress/ No. episodes of distress/month                                                                                                                    | MR + PQ Reports            | Monthly | >80%   |
|                                             | 2. No. of RT notes containing at least 1 recommendation (treatment or preventive, pharmacologic or non-pharmacologic), or otherwise providing the basis for not recommending anything / No. of distress episodes/month | MR + PQ Reports            |         | >90%   |
|                                             | 3. No. Times PC team communication with primary team documented/ No. episodes of distress/month                                                                                                                        | MR + PQ Reports            |         | >75%   |
| Response Team Training and clinical support | No. Providers with online + face-face training + evaluation/Total No. Providers/site                                                                                                                                          | Training logs              | Once    | >80%   |

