|                                             | No. consults to Listserv /No. episodes of persistent distress/month                                                                                                                                                           | PQ Reports + Listserv logs | Monthly | >80%   |

Abbreviations: MR: Medical record; RT: Response Team.

\*The Study Data Center will provide a set of smart text phrases to facilitate the documentation of intervention processes of local Response teams on the medical record. All palliative care notes from patients in the intervention arm will be abstracted and saved as pdf. Indicators will be built using pdfs.

Qualitative fidelity evaluation: All patients and parents, and a convenient sample of providers will be invited to participate in exit interviews that will inform fidelity assessment (see section 2.5.3). Providers selected to do these exit interviews will receive a \$50 gift card.

To monitor intervention fidelity, site RCs will collect all palliative care notes on intervention arm participants on a monthly basis, convert them to pdf, and send them to the PM using a send secure system (or a shared secure server such as Dropbox). The PM will receive monthly reports on the number of distress episodes reported through PediQUEST, among patients in the intervention arm, collect information on the use of listserv, and communicate with local PIs on an as needed basis to clarify information. With this information, the PM and VD (co-I) will build the indicators

and send monthly progress reports to the DSMB and SC (see section 5.1.2). Reports will be analyzed by the Data and Safety Monitoring Board to detect patterns of non-adherence or protocol deviations. If deviations in intervention processes are detected, they will be discussed with the local PI to decide whether retraining or site visits are indicated.

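### The three distress-response indicators in Table 2 divide event counts by episode counts, so they do not measure the share of distress episodes that got a response

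*Protocol*

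**What the plan says.** Section 2.3.2 presents Table 2 as the final list of fidelity indicators. Three of them concern the response to reported distress, each over a monthly period:

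- Contacts, target above 80%: the number of Response team contacts "of RT w/family or POT after a report of distress/ No. episodes of distress/month".
- Notes, target above 90%: the number of Response team notes with at least one recommendation, "or otherwise providing the basis for not recommending anything / No. of distress episodes/month".
- Communication, target above 75%: the number of times "PC team communication with primary team documented/ No. episodes of distress/month".

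For the denominator, the same section says "The PM will receive monthly reports on the number of distress episodes reported through PediQUEST". It describes no step that ties a contact or a note to a particular episode.

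Section 2.3.1.1 plans for more than one contact once distress is being managed. The team discusses its findings with the primary oncology team and, after a recommendation, "a designated member of the Response team will follow-up with the family to assess results and make further recommendations/contact P.O.T. as necessary". Section 2.3.3 adds regular encounters, at least monthly, whatever the level of distress.

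The last row of Table 2 sets a target above 80% for "No. consults to Listserv /No. episodes of persistent distress/month". Section 2.3.1.1 says that when the response to a plan is inadequate, "Response teams are encouraged to meet with local PIs to discuss the case". It describes the listserv as available and usable at any time.

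The fidelity data go to the DSMB and the steering committee (2.3.2) and into the process evaluation (4.3.2.4). They also bear on section 4.3.1: if "we identify substantial differences in fidelity across sites, we will evaluate effect modification by site".

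**The concern.** A percentage target reads as a proportion: above 80% suggests that fewer than one distress episode in five went without a contact. As written, the indicator is a rate of contacts per episode. Contacts with the family and contacts with the oncology team add up in one numerator, so an episode handled with several contacts offsets episodes that had none. The contacts indicator at least requires the contact to follow a report of distress. The other two do not state even that, so notes and communications from routine encounters could count.

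What is at stake is the trial's ability to show that a core part of the intervention was delivered. A site that concentrates its effort on a few families can look the same on these indicators as a site that answers every report. A site that handles several reports efficiently in one contact can look worse than it is.

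**Working it through.** The targets are values that the protocol sets, so there is no derived figure to reproduce. The check asks what share of episodes must be answered for each target to be met.

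**Inputs**
- Targets T from Table 2: contacts 80%, notes 90%, communication 75%.
- p = share of distress episodes with at least one response.
- k = mean number of events (contacts, notes or communications) per answered episode. The protocol does not give k; a range is shown as an assumption.

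**Formula**

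Indicator = events / episodes = p × k. The target is met when p > T / k, so just under 1 − T / k of episodes may go unanswered. Half or more of the episodes can be unanswered once k > T / 0.5.

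| Indicator | Target T | Share answered needed, k = 1 | k = 2 | k = 3 | k above which half can be unanswered |
|---|---|---|---|---|---|
| Contacts | 80% | 80% | 40% | 26.7% | 0.80 / 0.5 = 1.6 |
| Notes | 90% | 90% | 45% | 30% | 0.90 / 0.5 = 1.8 |
| Communication | 75% | 75% | 37.5% | 25% | 0.75 / 0.5 = 1.5 |

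**A month with 20 episodes (illustrative)**
- One contact per answered episode: 17 must be answered to exceed 80% (17/20 = 85%). The indicator then does what it appears to do.
- Two contacts per answered episode: 9 answered gives 9 × 2 / 20 = 90%. The target is met with 11/20 = 55% unanswered.
- Three contacts per answered episode: 6 answered gives 6 × 3 / 20 = 90%, with 14/20 = 70% unanswered.
- Three contacts, notes and communications per answered episode: 7 answered gives 7 × 3 / 20 = 105% on all three indicators, with 13/20 = 65% unanswered.

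**The opposite direction**

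Surveys are weekly, and one contact may deal with several reports of the same problem. If each contact covers two reports counted as two episodes, k = 1/2. Even with every report dealt with (p = 100%), the indicator is then 100% × 1/2 = 50% and misses the 80% target.

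The same ratio can therefore mislead in either direction, depending on a quantity that it does not report.

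**The case against.** The best defence is that Table 2 is shorthand. Its per-patient rows also divide a number of times by the number randomized to the intervention, and those plainly mean a share of patients. Percentage targets point to proportions. Section 2.3.2 mentions a full fidelity monitoring plan, discussed with the DSMB, which is not among the documents and may hold the counting rules. This makes it likely that a share of episodes was meant. It does not correct the protocol, which calls Table 2 final and gives no per-episode rule.

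It is also fair that k is assumed, that the problem disappears at k = 1, and that error can run both ways. The planned workflow makes more than one contact per answered episode plausible but does not establish how many.

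Several stronger readings are tempting, and the documents do not support them:

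- A reader might infer that distress would go unanswered and unseen. Reports go automatically to the family, the oncology team and a Response team member; regular meetings on active cases are encouraged; palliative care encounters are abstracted every four weeks; and exit interviews address fidelity.
- A reader might infer that these ratios mechanically trigger retraining or the site-by-intervention analysis. Section 2.3.2 has deviations discussed with the local PI, and section 4.3.1 names no indicator or threshold.
- A reader might infer that a null result could not be told apart from non-delivery. Palliative care notes for the intervention arm and weekly reports are stored, so delivery by episode could be worked out later.
- A reader might infer that a response was due within a week. The protocol sets no such deadline.

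On the listserv, the other side can say that section 2.3.1.1 offers it in addition to local PI meetings, and that section 2.3.2 counts its use among the activities the team incentive covers, estimated at twice a month. That supports expecting some use. It does not square optional wording with a target of one consult for more than 80% of persistent-distress episodes.

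**Conclusion.** The point stands in limited form. The contacts, notes and communication indicators are event-to-episode ratios that can exceed 100% and do not give the share of distress episodes that got a response. With an assumed two contacts per answered episode, the above-80% target is met once just over 40% of episodes are answered; with three, just over 27%; with one, the indicator works as it appears to. When one contact covers several reports, the indicator understates delivery.

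The effect falls on the fidelity reports to the DSMB and steering committee, the process evaluation, and the evidence on site differences that section 4.3.1 relies on. The primary analysis is not affected.

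The listserv row is a separate inconsistency and does not depend on k. A team that always takes the encouraged route of meeting the local PI, and never posts to the optional listserv, scores 0% against a target above 80%.

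**What to change.** In Table 2, redefine each of the three numerators as the number of distress episodes with at least one linked, documented contact (respectively a qualifying note, or a communication with the primary team). Keep all distress episodes as the denominator and keep the present targets. The sponsor should state the linkage rule: which documented events count towards which episode, and how one event that covers several reports is treated. If the full fidelity plan already counts this way, one sentence in Table 2 saying so is enough.

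Separately, reconcile the listserv target in Table 2 with the text in section 2.3.1.1 on meeting the local PI and optional listserv use.

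The cost is modest. The notes are already collected as PDFs and the reports are weekly, so no new data are needed, but events must be linked to episodes. The protocol is at version 17.1 (April 2022), with first enrollment listed as April 2018. Redefined indicators will therefore not be comparable with earlier monthly reports unless those are recomputed from the stored notes.
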